### Outcome measures

The primary and secondary endpoints were chosen based on DeCM [39, 40] and advance care planning trials [4, 5]. The primary endpoints are the prevalence and validity of advance healthcare planning documents (advance directives or others) and proxy burden at pre- vs. post-measurement. Secondary endpoints are decisional conflict, patient autonomy, and patient-proxy congruence in preference. Details about the measurement of endpoints are provided in Material section.

Furthermore, the following demographic and clinical variables will be recorded: age, gender, education level, psychiatric comorbidities, health literacy, and the need for autonomy in medical decision-making. Although only age has previously been shown to be associated with the primary endpoints [41], the additional variables will be collected to provide a comprehensive description of the study population and to enable exploratory analyses.

### Statistical methods

#### Required sample size and power analysis

The use of advance directives remains insufficiently widespread in Germany. Based on a German sample of 4,185 individuals between 50 and 90 years [42] and previous research with the target population [41], we anticipate a baseline prevalence of approximately 50% in our study population. Furthermore, the validity of existing advance directives is questionable in about 50% of cases [43]. The planned intervention will be considered practically relevant if this frequency increases by at least about 20-30 percentage points. Sample size calculations and simulations using the R package mixedpower showed that about 150 participants will be necessary to detect effects in the moderate range with sufficient power ($$> .8$$) in the focal effect of interest: i.e. the condition-by- time interaction in the (generalized) linear mixed-effects models (described in Statistical analyses section) both regarding our primary and secondary endpoints (see Outcome measures section).

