## Methods

### Participants

A total of $$N = 150$$ participants will be recruited in the period of March 2025 until January 2027 (see Required sample size and power analysis section for details on calculation and Recruitment section for recruitment details).

Inclusion criteria are a confirmed diagnosis of mild to moderate dementia (F00-F03) or mild cognitive disorder (F06.7), diagnosed by a physician specialised in neurology or psychiatry. The decision on whether to include a person with questionable capacity to consent will be based on a recommended procedure for involving non-consenting individuals in medical research [10]. Participants will be excluded from participation in cases of severe dementia (MMSE score $$< 11$$) and if lack of capacity to consent to study participation persists without an assisting proxy.

Additionally, every participating PwD will choose a trusted individual who will also participate in the study as proxy. If no such person is available, the PwD will still be considered for study participation.

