### Randomization

Participants will be randomly assigned to a control (DeCM as routine care) or treatment (DeCM + supported ACD) arm. Randomization will be stratified by gender and study arm. Because previous research indicated increased dropout rates in the supported ACD condition [9], stratified randomization by study arm will be conducted in a 2:1 (treatment:control) ratio, which is expected to result in approximately balanced groups of complete data in the two studyarms. During data collection, the ratio will be monitored and adjusted as needed to ensure balanced groups by the end of the study.

The allocations will be computer-generated using *R* package blockrand [13] with a block size of 9 for studyarm allocation. Separate randomization lists will be kept by gender as well as for each dementia care manager to ensure balanced recruitment ratios across individuals.

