#### Statistical analyses

Assessment of the prevalence and validity of advance directives will be based on Bayesian generalized linear mixed-effects models. Bayesian estimation is more appropriate than maximum likelihood for smaller sample sizes, when the priors are chosen carefully [44]. We will use probit models modeling the change in the probability of the presence and validity of advance directives over time given the experimental condition and possible covariates (see Outcome measures section).

Outcome variables in these models are a) the binary variable for presence of an advance directive (yes/no), and b) the binary variable for the validity of the advance directive in the sense that it was both voluntarily given and based on informed consent (yes/no). In these models, the condition-by-time interaction and the contrast (whether the pre-post change in the ACD + DeCM condition is more pronounced than in the DeCM condition) are of primary interest. Likewise, analyses of proxy burden and of secondary endpoints will be based on Bayesian linear mixed effects models. Scale scores based on 5-point Likert scale items usually justify the use of ‘normal’ linear mixed effects models. If this is not feasible, the outcomes will be modeled as (ordered) categorical. To avoid loss of sample size, and consequently loss of statistical power, missing data in all model variables will be multiply imputed where appropriate (see Exploratory statistical solution development for missing data and small sample sizes section).

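### The 150 to be recruited are also the 150 said to be needed for power above .8, yet the 2:1 rationale implies at most about 100 with complete data, and the protocol does not reconcile the two

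*Protocol article*

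**What the plan says.** Four statements in the protocol article bear on the point.

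- **Participants:** a total of 150 "participants will be recruited in the period of March 2025 until January 2027".
- **Required sample size and power analysis:** "about 150 participants will be necessary to detect effects in the moderate range with sufficient power" (above .8) for the condition-by-time interaction, for both primary and secondary endpoints. The effect is called moderate and given no number. On the directive outcome, "we anticipate a baseline prevalence of approximately 50% in our study population", and "The planned intervention will be considered practically relevant if this frequency increases by at least about 20-30 percentage points". Dropout is not mentioned.
- **Randomization:** allocation is 2:1 (treatment:control) because earlier work found more dropout under supported ACD. The ratio is "expected to result in approximately balanced groups of complete data in the two studyarms". It may be adjusted while the trial runs.
- **Statistical analyses:** "To avoid loss of sample size, and consequently loss of statistical power, missing data in all model variables will be multiply imputed where appropriate".

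The Discussion adds that attrition may shrink the sample and may be missing not at random.

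**The concern.** The recruitment target and the required number are the same figure, so no margin for attrition is visible. Yet the allocation ratio was chosen because substantial, unequal attrition is expected. A 2:1 allocation gives equal complete groups only if the treatment arm keeps half the proportion that the control arm keeps, so at least half of the treatment arm would lack complete data.

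The power statement covers every primary and secondary endpoint. If it refers to 150 analysable participants, it describes a larger trial than the one the Randomization section expects to analyse. A reader of an inconclusive result could then believe that a moderate effect had been given a better than 80% chance of detection when the chance was lower.

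**Working it through.** **The plan's own figure.** The simulation cannot be reproduced, because the article gives no numerical effect size, error level, T1-T2 correlation or dropout rate. A normal approximation for a difference in mean change (two-sided 5%, 80% power) returns N = 150 with complete data for an effect of 0.46 change-score SDs at 1:1, or 0.49 at 2:1. So 150 analysable participants is plausible for a moderate effect. Those two effects are back-solved and are not inputs from the document.

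**Step 1: complete data implied by the allocation.** From the document: N = 150, ratio 2:1, balanced complete groups. Randomised numbers are 150 × 2/3 = 100 and 150 × 1/3 = 50. Balance requires 100 × r_T = 50 × r_C, so r_T = r_C / 2.

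- Control retention 100%: 50:50, total 100, treatment-arm loss 50%.
- Control retention 90%: 45:45, total 90, treatment-arm loss 55%.
- Control retention 80%: 40:40, total 80, treatment-arm loss 60%.

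**Step 2: power for a continuous outcome.** Assumed, not in the document: d = 0.5 in raw SD, correlation ρ = 0.5, two-sided 5%.

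- Complete cases: SE = sqrt(2(1−ρ)(1/n_T + 1/n_C)).
- Likelihood under MAR with all 150 seen at T1: per arm, variance = (1−ρ²)/m + (1−ρ)²/n, where n is the number at T1 and m the number with T2. SE is the root of the sum over arms.
- Power = Φ(d/SE − 1.96). Detectable d at 80% power = 2.80 × SE (complete cases).

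| Complete T:C | SE, complete cases | Power | Power, MAR likelihood | Detectable d |
|---|---|---|---|---|
| 100:50 | .173 | .82 | .82 | 0.49 |
| 50:50 | .200 | .705 | .73 | 0.56 |
| 45:45 | .211 | .66 | .70 | 0.59 |
| 40:40 | .224 | .61 | .65 | 0.63 |

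Likelihood example at 50:50: (.75/50 + .25/100) + (.75/50 + .25/50) = .0375; SE = .194; .5/.194 = 2.58; power = Φ(0.62) = .73.

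**Step 3: dependence on the correlation, at 50:50 and d = 0.5.**

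| ρ | Complete cases | MAR likelihood |
|---|---|---|
| 0.4 | .63 | .66 |
| 0.5 | .705 | .73 |
| 0.6 | .80 | .82 |
| 0.7 | .90 | .91 |

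**Step 4: changing the ratio.** With the same expected retention and 1:1 allocation, 75:75 becomes about 37.5:75 complete. SE = sqrt(1/37.5 + 1/75) = .200, the same as 50:50. Changing the ratio does not recover the loss. Only better retention would.

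**Step 5: presence of a directive.** From the document: baseline about 50%, relevant increase 20-30 points. Assumed: control stays at 50%, T2 proportions compared alone, two-sided 5%.

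- 50% vs 70% at 50:50: (0.2 × √50 − 1.96 × √0.48) / √0.46 = 0.08; power = Φ(0.08) = .53. At 100:50 with no loss it is .67.
- 50% vs 80% at 50:50: power .89.

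A simulated difference in pre-post change between arms, closer to the planned interaction, gives at 50:50 .37-.72 for 70% and .69-.95 for 80%, as the latent T1-T2 correlation goes from 0.3 to 0.9.

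**The case against.** The strongest reply is that the power section never says that its 150 is an analysable number. It reports simulations, and a simulation can include 2:1 allocation and dropout. A reader might infer that the stated power is not delivered. The documents do not support that, because the effect size, correlation and dropout behind the figure are not given. This part of the reply stands.

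Other replies stand in part.

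- *Complete data is undefined.* Table 1 lists extra measurements in the treatment arm, and the intervention is only an offer, so a person who declines ACD could still supply T1 and T2 outcomes. The figure of 100 therefore follows from the plan's expectation of balance. It does not prove that half of the treatment arm will lack T2.
- *The planned models use more than complete cases.* True, but the gain is small: .705 to .73 at 50:50. Under MAR, imputation from the same variables cannot be expected to do better. Strong auxiliary variables could add something. The Discussion itself allows for MNAR.
- *The imputation sentence is fair when set against deleting incomplete records.* It is, and it is qualified by where appropriate. Read as avoiding the loss of power, it still promises too much for missing T2 outcomes.
- *The ratio can be adjusted.* At the expected retention this does not help (Step 4).

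A reader might also infer that validity can be analysed only in holders of a directive, with far fewer people. The article gives a yes/no variable and does not exclude coding non-holders as having no valid directive, so no figure is attached to that here.

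**Conclusion.** The point holds as a failure to reconcile three statements: 150 recruited, about 150 necessary, and an allocation whose rationale leaves at most about 100 with complete data. It is not a demonstrated error in the simulation.

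Its size is conditional. If 150 means analysable participants, power for d = 0.5 at correlation 0.5 is about .61-.70 on complete cases or .65-.73 by likelihood, against .82 at 100:50. At 50:50, about .8 is still reached with a correlation near 0.6 or an effect near 0.56. At the plan's lower relevance limit (50% vs 70%, T2 only) power is about .53 at 50:50. Part of that shortfall is present before any loss, and the upper limit (80%) gives .89.

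Proxy burden, a primary endpoint, could have fewer pairs still, since the Participants section admits people without a proxy. The document gives no number for this.

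**What to change.** Keep N = 150 and make three changes.

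1. In the power section, say whether 150 is before or after attrition. Rerun the simulation with the 2:1 allocation and the expected dropout per arm. Report power and detectable effect at the expected 80-100 complete pairs, separately for each primary and secondary endpoint, with proxy burden based on dyads that have a proxy. As a guide, detectable d at correlation 0.5 is 0.56 with 100 pairs, 0.59 with 90 and 0.63 with 80.
2. If dropout was already simulated, state the dropout per arm, the allocation and the completer numbers used. No rerun is then needed for endpoints that the simulation covered.
3. In Statistical analyses, say that multiple imputation limits the loss of power, not that it avoids it.

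The cost is some rewording and at most one rerun of an existing simulation. No further participants are needed. If dropout was left out before, the stated power will be less favourable.

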#### Statistical analyses

Assessment of the prevalence and validity of advance directives will be based on Bayesian generalized linear mixed-effects models. Bayesian estimation is more appropriate than maximum likelihood for smaller sample sizes, when the priors are chosen carefully [44]. We will use probit models modeling the change in the probability of the presence and validity of advance directives over time given the experimental condition and possible covariates (see Outcome measures section).

Outcome variables in these models are a) the binary variable for presence of an advance directive (yes/no), and b) the binary variable for the validity of the advance directive in the sense that it was both voluntarily given and based on informed consent (yes/no). In these models, the condition-by-time interaction and the contrast (whether the pre-post change in the ACD + DeCM condition is more pronounced than in the DeCM condition) are of primary interest. Likewise, analyses of proxy burden and of secondary endpoints will be based on Bayesian linear mixed effects models. Scale scores based on 5-point Likert scale items usually justify the use of ‘normal’ linear mixed effects models. If this is not feasible, the outcomes will be modeled as (ordered) categorical. To avoid loss of sample size, and consequently loss of statistical power, missing data in all model variables will be multiply imputed where appropriate (see Exploratory statistical solution development for missing data and small sample sizes section).

### Methodological side projects

#### Exploratory statistical solution development for missing data and small sample sizes

Missing values in randomized controlled trials commonly pose challenges for accurate statistical inference, especially when sample sizes are (very) small, which is commonly the case in dementia research. The emerging challenges, such as loss of power and model identification issues, can be addressed through methods such as multiple imputation (MI). Previous research found that MI under *Missing At Random* (MAR) could yield acceptable inferences even for small-sample-sizes [45, 46], and could outperform other missing data handling techniques in small sample scenarios [47].

However, the particular approach that is being used heavily influences the obtained results, and adopting the default methods and settings of standard MI software might not be the best option available [48, 49]. Until now, there is little research regarding these consequences in the binary outcome context, where the required sample size further depends on the imbalance of event rates in the outcome. While MI has been found to be superior to other methods in the context of logistic regression [50], the question remains whether a logistic MI model is still feasible when sample size is very small.

Using Monte Carlo simulations, this subproject aims to investigate the performance of logit and probit MI models to handle missing values in small sample size scenarios. Looking beyond common MI solutions, we will also explore fully Bayesian analytical approaches as well as maximum likelihood approaches. The overall aim is to provide practical guidelines regarding how to properly treat missing data in small sample size scenarios and to apply them to missing value handling in the main study.

#### Interrater reliability of Capacity-to-Consent-Judgments of dementia care managers vs. psychotherapists

In the current study, dementia care managers will assess the capacity to consent for (or against) the creation of an advance directive. The extent to which dementia care managers align with physicians and psychotherapists in assessing the capacity to consent (interrater reliability) will be examined in this side project with two sub-studies.

In the first sub-study of the interrater side project, the conversations conducted by dementia care managers for the assessment of capacity to consent will be recorded if agreed to by the PwD; a physician or psychotherapist will then provide a second judgment on capacity to consent based on the recordings. The participating physicians and psychotherapists are recognized experts in capacity assessment.

The second sub-study of the interrater side project will assess inter-rater agreement between nursing professionals and physicians or psychotherapists in an online study. Similar to the study of Haberstroh & Müller [51], it will utilize a case vignette of an individual with mild dementia. The presentation and structure of the case will follow the guideline for assessing capacity to consent, developed in collaboration with the American Bar Association and the American Psychological Association [52]. In this online study, participants will first be presented with the criteria for capacity to consent, then they will be shown a case vignette and asked to assess the patient’s capacity to consent based on the vignette.

### Quality control

For quality assurance and control, all study personnel will receive training in content-related, methodological, ethical, legal, and organizational aspects [53]. All dementia care managers have undergone comprehensive ACD-training provided by experts, equipping them with specific knowledge and skills required to conduct supported ACD with the target population. A small pilot study ($$n < 5$$) will be conducted and evaluated prior to the main study so that any required modifications can be incorporated into the manual of operations. Necessary changes to established procedures will be justified, documented and communicated to all study personnel in a timely manner. Any amendment will be submitted to the responsible ethics committee.

#### Data management

##### **Data collection**

Data collection conducted by the dementia care managers will be computer-assisted using the proprietary software of the German Center for Neurodegenerative Diseases in Greifswald and will be stored on the Center’s local servers. For the subpopulation of participants who create an advance directive as part of the study, audio recordings of the approximately 20-minute interview section to assess capacity to consent (CAT-AD) will be made using dedicated digital voice recorders. These recordings will be re-evaluated by the psychotherapists from the research team to assess inter-rater reliability and to ensure quality control of the assessment.

All personnel managing personal data as part of the research project will be made aware of applicable legal requirements and potential risks. Before the start of fieldwork, those involved in data collection will be thoroughly prepared, trained and their activities will be constantly monitored. Data collection will be accompanied by continuous data monitoring and standardized reporting. Monitoring will focus on aspects like missing values, implausible values, and value distributions. The study has been registered in the German Clinical Trials Register (DRKS Trial no. DRKS00036478) and this protocol was written following the SPIRIT guidelines (see Additional file 2). External quality will be further assured through external expert advice on ethics (see Ethical considerations section).

##### **Confidentiality, data access and storage**

Personal data will be anonymized before being entered into the project database and all forms of data processing will be conducted in compliance with the EU General Data Protection Regulation (GDPR) and applicable national data protection laws, ensuring data protection. Project data will be retained at the principal investigators’ institutes for at least 10 years after the funding period ends. Anonymized research data will be archived for long-term preservation (e.g., via the research data center at the Leibniz Institute for Psychology) and (as far as possible) made accessible to interested parties upon reasonable request.

The audio recordings will be stored in the university cloud, password-protected, and deleted after evaluation. They will only be accessible to a limited group of individuals (responsible dementia care manager, study physician/psychotherapist). In the case of conflicting judgments, the audio file will be given to a third qualified decision-assistance person (study physician or psychotherapist) for independent assessment.

### Ethical considerations

The study has been reviewed and approved by the Ethics Committee of the Medical Council Westfalen-Lippe Council Westfalen-Lippe (trial no. 2024-767-f-S). A list containing the items of the WHO Trial Registration Data Set was completed (see Additional file 3). In case of any relevant changes to this protocol, both the study registry and the ethics committees will be informed and asked for approval.

#### Informed consent

The capability of providing informed consent can be an ethical issue in individuals with dementia. In accordance with the German AWMF (Association of Scientific Medical Societies in Germany) S2k guidelines for medical procedures (“Einwilligung von Menschen mit Demenz in medizinische Maßnahmen” [17]), participants will be supported as far as possible (e.g. through use of keyword lists, plain language). In questionable cases, consent by proxy will be considered, but the participant’s assent will still be required. In such cases, the decision on whether to include a person with questionable capacity to consent will be based on a recommended procedure for including non-consenting individuals in medical research [10].

Following European Commission Guidelines, we will carefully design informed consent forms and processes as well as information sheets based on the results of our previous research [54, 55] and on already existing documents of the RoutineDeCM project [16].

#### Possible harm

PwD in the intervention group will receive two additional appointments including decision-making situations, which can be stress-inducing for the PwD. To minimize adverse events and negative psychological symptoms, tailored support strategies will be used. To avoid overload, the process of creation of advance care documents will be spread over two appointments. Other than this, no possible harm or adverse events are expected. Treatment and care will follow current guidelines and be supervised and coordinated by clinical experts. The dementia care managers are specifically trained and qualified for the tasks involved in conducting the intervention. This includes an emergency plan, phone availability of supervisors during household visits as well as intense training by psychotherapists to handle adverse events. Case conferences with clinical supervisors will be conducted on a regular basis, enabling the dementia care managers to discuss and receive consultation for experiences made in the household.

